**Figure 1 F1:**
[figure not shown]
**Instrumentation of objects.** (**A**) A coffee mug is instrumented with the motion sense mouse using Velcro strips. (**B**) A turning knob is instrumented with the mouse using a wooden block, dowel, rubber pad and Velcro strips.

Common objects of daily life have different physical, functional and ergonomic properties. Taking advantage of these properties, objects can be selected to train dexterity, graded mobility in metacarpal phalangeal, interphalangeal and wrist joints, or strengthen finger and wrist muscles. A framework (Figure 2) has been developed for selecting therapeutic objects for specific therapeutic values. The application allows manipulation of objects of any shape (cylindrical, spherical, conical and rectangular) or size (small, medium and large). A wide range of small to large objects can be used to train dexterous functions involving the use of two, three or four fingers or the whole hand, wrist and forearm in order to improve task accuracy, precision and movement quality/efficiency. Training of such skills are expected to emulate many daily functional activities such as holding/manipulating fine, medium and large objects, and cylindrical or spherical objects, turning a door key, doing up buttons, or pulling up/down zippers during dressing. A bottle cork, salad tongs, door knob, key, and fine beads are a few objects that can be selected to train fine manipulations. Large-sized balls, large–medium-sized scissors, a coffee mug, large–medium–small diameter paper rolls and sponge foam cylinders can be selected for gross manipulations. In addition to dexterity, strength training needs to be included because hand strength is also needed to perform many daily tasks requiring a strong grip, such as carrying heavy items, opening tight jars and turning large knobs.

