##### Therapeutic values: strengthening

6. Object selected: half-filled jug

Method: the jug is held with the whole hand around the handle and the task requires tilting the jug sideways up or down, simulating pouring activity.

7. Object selected: a dumbbell

Method: a dumbbell held with the whole hand and forearm supinated or pronated can be used for graded strengthening of wrist flexors or extensors (Figure 3D).

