### Outcome measures

#### Primary outcome measure

The primary outcome measure will be the Arthritis Hand Function Test, an 11-item performance-based test that measures grip and pinch strength, dexterity, applied strength and dexterity in people with arthritis. Test–retest reliability of the Arthritis Hand Function Test measured by the intraclass correlation coefficient in 20 individuals with RA ranged from 0.53 to 0.96; inter-rater reliability ranged from 0.89 to 1.0. Test–retest reliability in 26 individuals with OA ranged from 0.7 to 0.96; inter-rater reliability ranged from 0.99 to 1.0 [38,39].

The peg-board dexterity test measures the time taken in seconds to place and remove nine pegs into the nine holes. Applied dexterity is the total time taken (seconds) to complete the following tasks: lacing a shoe, tying a bow, fastening/unfastening four buttons, fastening/unfastening two safety pins, cutting putty with a knife and fork, and manipulating coins into a slot.

Applied strength will be measured by the total number of soup cans lifted in a tray and the volume (ml) of water lifted in a pitcher.

Grip strength of the dominant hand will be clinically tested using a handheld dynamometer (Biometrics isometric hand dynamometer G100; Biometrics Ltd, Cwmfelingach, Gwent, UK). Grip strength will be recorded in kilograms and the best score out of the three consecutive trials will be used for analyses. Similarly, three-point pinch strength will be measured using a pinch meter (Biometrics precision pinch meter P200; Biometrics Ltd).

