**Figure 5 F5:**
[figure not shown]
**Parsed movements from a random game play.** Outcome measures derived from episodic game play are shown.

The tool is also embedded with two separate numerical verbal pain and stiffness scales. The pain scale ranges from 0 (no pain) to 10 (unbearable) and stiffness from 0 (none) to 10 (cannot move). These scales will appear in sequence on the computer monitor before and immediately after each pre-timed sinusoidal tracking or the random game. Participants will be asked to verbally rate their pain and stiffness intensity before and after each manipulation task. The study staff record them, and they will be automatically saved along with the user motion data.

The tool will be used to evaluate quality and spatio-temporal accuracy during four manipulation tasks with objects such as a salad tongs, a small bead, jug and a turning knob. These objects are selected to represent a diverse range of manipulation tasks needing different functional requirements of handling. Note: in order that there is no practice effect, these four objects will not be included for the experimental group. Our previous pilot work has reported that the jug and salad tongs were difficult to manipulate in people with RA or OA. So these two manipulation tasks will be evaluated in predictable tracking mode with a duration of 30 seconds. Skill and efficiency of the other two manipulations will be evaluated while playing the random game for 90 seconds. Evaluation of all four tasks may take approximately 7 to 10 minutes.

The measures derived from both game modes of the computer-based hand assessment tool are as follows: predictable tracking – task performance (coefficient of determination), spatio-temporal accuracy measures (temporal accuracy, amplitude consistency), pain and stiffness intensity; and episodic (random) game – success rate (number of target hits), movement skill (average motor initiation time, average motor response time), movement efficiency (movement path length), and pain and stiffness intensity.

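### The jug is reserved for assessment to prevent practice, yet it is on the experimental training list, so one of the four exploratory tool tasks can be biased in that arm's favour

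*Protocol article*

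**What the plan says.** Under Secondary outcome measures (text after Figure 5), the computer-based tool is to evaluate movement "during four manipulation tasks with objects such as a salad tongs, a small bead, jug and a turning knob". The same paragraph gives the safeguard: "in order that there is no practice effect, these four objects will not be included for the experimental group". It then says that the jug and the tongs proved difficult in earlier pilot work: "So these two manipulation tasks will be evaluated in predictable tracking mode with a duration of 30 seconds". The bead and the knob are assessed in the random game. The same section designates the tool as exploratory.

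Under Interventions, Experimental group, the training objects are numbered 1 to 7. Item 6, under Therapeutic values: strengthening, is "Object selected: half-filled jug", with the method that "the jug is held with the whole hand around the handle and the task requires tilting the jug sideways up or down". The introduction to that list says that the movements made with each object drive the game cursor.

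The control programme (Control group; Home program training sessions) consists of finger and wrist exercises, putty and a dumbbell. It contains no jug, no motion mouse and no game.

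The Background, describing the platform in general, adds: "A bottle cork, salad tongs, door knob, key, and fine beads are a few objects that can be selected to train fine manipulations".

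**The concern.** The protocol sets itself a rule, that no assessed object is trained, and its own training list then breaks the rule for one object. Because only the experimental arm can train with a jug, the breach is not balanced between arms. Any gain from practising with the tested object would raise that arm's jug tracking results (coefficient of determination, temporal accuracy, amplitude consistency). It would do so both in its pre-to-post change and in the post-intervention comparison with controls.

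The trial is meant to supply preliminary effect estimates. A reader who relies on the stated safeguard would take a jug-task difference as transfer to an untrained object, when for some participants it may be improvement on a trained one. The two interpretations have different implications for a later trial.

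**Working it through.** No power or sample size figure is involved, so the check is a comparison of lists.

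**Step 1. The lists.**

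| List | Source | Objects |
|---|---|---|
| Assessment | Secondary outcome measures | tongs, bead, jug, knob (4) |
| Experimental training | Experimental group, items 1 to 7 | key, bottle cap, sport ball, plate or board, drinking glass, half-filled jug, dumbbell (7) |
| Control training | Control group; Home program training sessions | putty, dumbbell, free hand exercises |

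**Step 2. Overlap.** Assessment and experimental training share one object, the jug. Assessment and control training share none.

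**Step 3. Share of the tool affected.** 1 of 4 tasks = 25%. Predictable tracking has two tasks (jug and tongs), so 1 of 2 = 50% of that mode. The random game (bead and knob) has no overlap with the numbered list.

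**Step 4. Does the wording leave a way out?** The assessment objects are introduced with *such as*, which might suggest that they are only examples. But the safeguard then refers to these four objects, and the jug is named again when the tracking mode is assigned. The list is therefore fixed, and the jug is on it.

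**Step 5. How many participants could be affected?** The article does not say. Objects are personalised by clinical judgement (Six-week home program), and Table 1 gives 3 to 4 objects per participant in the first two weeks, 4 to 5 in weeks 3 to 4 and 5 to 6 in weeks 5 to 6. If objects were drawn evenly from the seven listed, which is purely an assumption, the share using the jug would be:

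- first two weeks: 3/7 to 4/7 = 43% to 57%
- weeks 3 to 4: 4/7 to 5/7 = 57% to 71%
- weeks 5 to 6: 5/7 to 6/7 = 71% to 86%

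Selection is not an even draw, and the list is described as a few examples, so the defensible range is 0 to 100%. Selection by need could favour the jug, since the protocol reports it as hard to handle for these patients, but that is an inference.

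**Step 6. Outcomes not touched.** The Arthritis Hand Function Test and the DASH do not use the tool. The Statistical analysis plan section names test items, DASH and completed sessions for analysis; it does not name tool measures.

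**The case against.** The strongest reply concedes the contradiction and disputes its weight. The tool is exploratory, the trial is a pilot of 30 with no formal sample size calculation, and one task of four is involved. The training list is illustrative and objects are personalised, so possibly no one trains with the jug. All of this stands. It lowers the severity and means that the jug task *can be* biased, not that it *is*. It does not remove the conflict, because both statements are explicit and staff could follow either.

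Several stronger readings are tempting but not supported:

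- **All four tasks are compromised.** A reader might infer this from the Background sentence naming tongs, knob and beads as trainable. That sentence describes what the platform permits; the later, trial-specific exclusion narrows it. Among the numbered training objects only the jug overlaps.
- **The jug exposure is 480 minutes.** Table 1 gives 4 sessions × 2 weeks × (15 + 20 + 25) = 480 minutes if durations are per session. That is total exercise time over all objects, including strengthening, and not jug time.
- **The primary outcome is contaminated.** Its applied-strength part includes "the volume (ml) of water lifted in a pitcher", which resembles handling a jug. But the item measures volume lifted, the training is tilting, and carry-over to everyday tasks is what task-oriented training intends.
- **Both arms need added familiarisation with the assessment game in the training sessions.** Those sessions follow the baseline visit, so this would add practice between the pre and post measurements and inflate the planned within-group changes.

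One wider point survives in part. Training uses commercial games and the tool is a purpose-built paddle game, and controls also meet the tool at baseline, because secondary outcomes are assessed then. Even so, only the experimental arm has six weeks of driving a cursor with the motion mouse. Excluding objects cannot remove that familiarity, whose size is undocumented.

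**Conclusion.** The contradiction is real and the text is wrong as written. One of the four tasks of the exploratory tool, and one of its two predictable-tracking tasks, can be biased in favour of the experimental arm for participants who train with the jug. Their share is unknown (0 to 100%), and so is the size of any practice gain. The primary outcome and the DASH are not directly affected. Severity is moderate.

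The conclusion assumes that the training jug and the assessment jug are similar enough for practice to carry over. The article does not describe the assessment jug's filling or the movement required, but its own exclusion rule treats the object as what matters. The claim that practice is absent can at most refer to object-specific practice, and as the lists stand it fails even there for the jug.

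**What to change.** 1. Reconcile the strengthening list under Experimental group with the exclusion under Secondary outcome measures, so that the training and assessment lists share no object. State that the exclusion binds whoever selects the personalised objects. Which objects are used therapeutically is for the investigators to decide; the statistical requirement is only that the lists be disjoint.
2. Make the Background examples consistent, for instance by noting that objects reserved for assessment are not used for training in this trial.
3. Check the treatment records, which already hold the exercises prescribed to each participant. If anyone has trained with the jug, leave the jug task out of the between-group tool comparison, or report it separately with the number exposed and that caveat.
4. Limit the practice statement to object-specific practice, and say that only the experimental arm trains with the motion mouse and computer games.

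The assessment object should not be swapped mid-trial: the article gives the trial status as ongoing, and a change would break pre-to-post comparability for participants already assessed at baseline.

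The cost is a few sentences of text and a look through existing records. No new data collection is needed. If the jug task is excluded, predictable tracking rests on the tongs task alone, which is a modest loss for an exploratory measure.

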**Figure 4 F4:**
[figure not shown]
**Objective variables of the predictable tracking task.** (**A**) Coefficient of determination of user motion trajectory. Bold lined waveform, user motion signal; thin line, reference waveform for a manipulation task. (**B**) Temporal accuracy. Bold lined waveform in the top plot, reference waveform; light shading, user motion signal for a manipulation task. A maximum and minimum point on the up and down cycles of the user signal is shown. The time taken to reach maximum and minimum points for each movement cycle is compared between the two signals. (**C**) Amplitude consistency. An arbitrary line drawn on a user motion signal represents amplitude consistency in upward and downward directions.

Temporal and amplitude accuracy measures will be determined at the turning points of each cycle of the user motion trajectory (Figure 4B,C). For temporal accuracy, the time taken to reach maximum and minimum points of each cycle of the user motion will be subtracted from the time of the respective target cursor motion maximum and minimum. Average absolute temporal accuracy (in milliseconds) of maxima and minima for all of the cycles will thus be determined. The amplitude consistency of the object motion will be determined by the coefficient of variation of the average movement amplitude in both directions.

For episodic (random) play, the goal of this game mode is to move the paddle (game sprite) to hit the random targets moving vertically top to bottom or horizontally from left to right of the computer screen. The game will be played using an instrumented object that generates a logged game file to record the time index and coordinates of each game target and to record the position coordinates of the game paddle that slaves to player’s movements (representing the respective object manipulation task). The data will then be processed and analyzed in Matlab.

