Each one minute of game play can provide around 30 to 40 player movements (multiple events). These movements can be parsed and sorted by movement direction and movement amplitude/speed. Figure 5 shows the parsed movements in a gaming session of 2 minutes. Different features of the player’s movements provide a basis for objective quantification of variables such as: number of hits/misses of the paddle on the random targets; time measured between the appearance of the target to the start of the paddle movement (motor response time); time taken to reach the target location from the paddle initial location (movement execution time); and movement path length from start to end of all gaming events.

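### Random-game efficiency is raw path length and success rate is a raw hit count, although targets are random, so a participant who tries for fewer or nearer targets can look more efficient

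*Protocol article*

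**What the plan says.** The Secondary outcome measures section of the protocol article describes a computer paddle game, designated exploratory, with a tracking mode and a random mode. In the random mode the player moves the paddle to "hit the random targets moving vertically top to bottom or horizontally from left to right of the computer screen". Two of the four test objects are "evaluated while playing the random game for 90 seconds".

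The closing list of derived measures in that section gives, for the random game, "success rate (number of target hits), movement skill (average motor initiation time, average motor response time), movement efficiency (movement path length"). The timing measures in this list are averaged; hits and path length are not. A little earlier the section describes path length as "movement path length from start to end of all gaming events", and says that the game can be scored for both hits and misses. The game file stores the time and coordinates of each target and the position of the paddle.

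The Statistical analysis plan section names the outcomes to be tested. No random-game measure is among them.

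**The concern.** A rate needs a denominator, and efficiency needs a comparison of what was done with what was required. The article gives neither for these two measures, in the one game mode where the task itself varies by chance from play to play. The tracking-mode measures do not share the problem: they are scaled against a known target or expressed as a coefficient of variation.

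Two things follow for path length. First, chance placement of targets enters every participant's score as noise. Secondly, path length mixes wasted movement with the amount of movement attempted. If training makes participants go for more targets, or more distant ones, path lengthens and apparent efficiency falls while hits rise. Path length is the only efficiency measure listed for this mode, so a pilot meant to give preliminary estimates could report a change in efficiency of the wrong sign.

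**Working it through.** There is no stated figure to reproduce. The check is a reading of the definitions followed by an illustration.

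**Reading.** Path length over the whole run of gaming events reads most naturally as a session total. A per-event length is not ruled out, so both are examined.

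**Inputs.** The game length of 90 seconds is from the article. The number of targets per game is not stated. I use 45 and 60 purely as illustrative sizes; they are 1.5 minutes times the two ends of the article's movement rate. Further assumptions of mine: a one-dimensional screen of width 1, targets placed uniformly at random, and a paddle that starts mid-screen and stays at the last target reached.

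**Step 1: straight mover who reaches every target.** The expected distance between two uniform points is 1/3, and from mid-screen to the first target it is 1/4. Expected path for n targets = 1/4 + (n − 1)/3.
- n = 45: 0.25 + 44/3 = 14.9 screen widths
- n = 60: 0.25 + 59/3 = 19.9 screen widths

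Simulation (20,000 games) gives the same means. At n = 45 the standard deviation from target position alone is 1.7, so the coefficient of variation is 1.7/14.9, about 11%, with a 95% range of 11.7 to 18.4. Dividing by the number of events rescales mean and standard deviation alike, so the 11% also applies to a per-event length.

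**Step 2: effect of attempting fewer targets (n = 45, 5,000 games).** The selective player ignores targets more than half a screen away.

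| Player | Path | Hits of 45 | Path per hit | Path / required distance |
|---|---|---|---|---|
| Attempts all, straight | 14.9 | 45 | 14.9/45 = 0.33 | 1.00 |
| Attempts all, 20% excess | 17.9 | 45 | 17.9/45 = 0.40 | 1.20 |
| Selective, straight | 7.6 | 34 | 7.6/34 = 0.22 | 1.00 |
| Selective, 20% excess | 9.1 | 34 | 9.1/34 = 0.27 | 1.20 |
| Never moves | 0 | 0 | undefined | undefined |

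On total path, the selective player with 20% waste (9.1) looks better than the perfect player (14.9). On path per hit the order is the same (0.27 against 0.33), because nearer targets were chosen. Suppose a participant moves from the fourth row to the first after training. Wasted movement disappears and hits rise from 34 to 45, yet total path lengthens by 14.9/9.1 − 1 = 64%. At n = 60 the pattern holds: 12.1 against 19.9.

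**Step 3: the ratio.** Total path over reached targets divided by total required distance for the same targets separates the straight mover (1.00) from the wasteful one (1.20), whichever targets are attempted. It says nothing about how many were reached, so the hit proportion must stand beside it: 45/45 = 100% against 34/45 = 76%.

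**The case against.** The article may only be summarising. The measures in the closing list stand in brackets, misses are mentioned elsewhere, and the computing routines are not shown. Movements are also said to be sorted by direction and amplitude, which would be one way to handle near and far targets. Nowhere is path length called a sum, nor a shorter path called better. Hits, times and path are reported together, so a participant who hardly moved would show few hits.

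Part of this stands. The session total is the natural reading but not a certain one, and the direction of scoring is implied only by the label. Reading path beside hits would expose an extreme case. It would not rescue the efficiency measure for ordinary participants, because neither raw measure separates wasted movement from movement attempted. Nor is this simply absent detail: the article states which quantity represents success and which represents efficiency, and averages the times in the same list.

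A stronger reading is tempting for the hit count. The article says "Each one minute of game play can provide around 30 to 40 player movements (multiple events"), so a reader might infer 45 to 60 scoring chances in 90 seconds, and hence a hit count that varies by a third with no change in skill. The article does not support that. The figure counts movements made by the player, not targets presented, and making fewer movements may itself reflect performance. If every game presents the same number of targets, the hit count and the hit proportion differ only by a constant.

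**Conclusion.** The point holds for path length. As defined, it depends on where targets fall under either reading, and on how many are attempted if it is a session total. The simulated sizes (about 11% variation from position alone, and the reversed ranking) rest on my assumed screen, target placement and number of targets. They show the mechanism and do not predict its size in this trial. For the hit count the point is conditional: it matters only if the number of targets presented differs between games.

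A reader might infer that random targets bias the comparison of arms. They do not, because both arms meet the same random mechanism, so that component is noise. Distortion can arise only if the interventions change how many targets, or which ones, participants attempt.

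Priority is low. The tool is exploratory, its measures are not among the named tests, and the Arthritis Hand Function Test is untouched. The correction is still worth making before analysis, because a pilot of 30 participants has little room for avoidable noise.

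**What to change.** Reword the two definitions in the Secondary outcome measures section:

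- **Success rate:** hits/(hits + misses), with every presented target that is not hit counted as a miss, including those not attempted.
- **Movement efficiency:** total path length over events in which the target was hit, divided by the total straight-line distance from paddle start to target for those same events. Because the targets move, state which target position is meant. Report it always alongside the hit proportion.

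Use a ratio of sums rather than an average of per-event ratios, which becomes unstable when the paddle starts close to the target. Restrict it to hit targets: over all events, a motionless player would still get the best score.

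The cost is minor Matlab work. Hits, misses and coordinates are already available, so no new data or participant time is needed. The one drawback is that efficiency is then conditional on targets reached, which is why the hit proportion must accompany it.
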